## Abstract

**Background:**

Insomnia is among the most prevalent of the sleep-related disorders. Insomnia disorder is associated with a brain hyperarousal state manifested by abnormal regional brain activity and resting state functional connectivity. Acupuncture improves sleep quality and modulates the hyperarousal state; however, the underlying neurobiological basis for improved sleep quality is poorly understood. The purpose of this clinical trial is to study the efficacy of acupuncture in the treatment of insomnia disorder. In addition, the neural mechanism by which acupuncture affects insomnia disorder will be explored using resting-state functional magnetic resonance imaging (rs-fMRI) and neuropsychological parameters.

**Methods and design:**

A randomized, patient- and assessor-blinded trial will be conducted. We will randomize (in a 1:1 ratio) 60 eligible patients with insomnia disorder into a real acupuncture group or a sham acupuncture group. Interventions will be administered three times per week over a 4-week period, with an 8-week follow-up period. The healthy control group will consist of 30 age- and sex-matched healthy individuals who sleep well without any treatment intervention.

All participants will undergo neuropsychological and rs-fMRI evaluations. The change in Pittsburgh Sleep Quality Index (PSQI) scores is the primary outcome parameter. The secondary outcome parameters include the Hyperarousal scale (HAS), rs-fMRI measurements, the Fatigue scale-14 (FS-14), the Hamilton depression scale (HAMD), the Hamilton anxiety scale (HAMA), a sleep diary, and an actigraph.

Assessment of all parameters will be performed at baseline, post-treatment, and during follow-up. Analyses will be implemented based on intention-to-treat.

**Discussion:**

The study results will be used to clarify the effectiveness and elucidate the mechanism by which acupuncture improves sleep quality in patients with insomnia disorder.

**Trial registration:**

Chinese Clinical Trials Register, ChiCTR1800015282. Registered on 20 March 2018.

## Background

Insomnia, which affects 10 to 15% of the population [1], is characterized by problems falling asleep, remaining asleep, or obtaining refreshing sleep, and is accompanied by impairments of daytime functioning [2]. However, the pathophysiology of insomnia is still under investigation. The most compelling hypothesis for insomnia is the hyperarousal model [3], which states that somatic, cognitive, and brain activation are increased in patients with insomnia [4].

The first-line therapies for insomnia are pharmacologic intervention with hypnotic medications and cognitive behavioral therapy. However, many patients are troubled by the side effects of medications, including lingering daytime sedation, cognitive impairment, and medication dependence. Psychotherapy is time-consuming and depends on the availability of trained therapists [5]. These factors lead to a low compliance rate for insomnia therapy [6]. Therefore, some patients have sought alternative treatments. Acupuncture, a critical component of traditional Chinese medicine, may relieve the symptoms of insomnia [7–10]. Nevertheless, the underlying neural basis for the effects of acupuncture remains largely unknown.

Recently, neuroimaging investigators have become interested in the spontaneous low-frequency fluctuations in brain activity when at rest. Studying these low-frequency fluctuations may help in elucidating the brain’s intrinsic functional organization to aid in understanding the neurobiological mechanisms of insomnia and its treatment [11]. For instance, enhanced functional connectivity between the amygdala and the premotor and sensorimotor cortex occurs in patients with insomnia disorder. The amygdala is closely related to fears, depression, and anxieties. Therefore, insomnia disorder may be related to increased negative emotional memory activity [12]. The insula is connected to other parts of the emotional circle [13], and anterior insula interactions with salient networks have been detected [14]. In a study by Dong, increased whole brain positive connectivity detected in patients with insomnia disorder was associated with a hyperarousal state [15]. Furthermore, regional homogeneity (ReHo) increased in the left insula of patients with insomnia disorder that positively correlates with Self-Rating Anxiety Scale scores [16]. Taken together, research using data from resting-state functional magnetic resonance imaging (rs-fMRI) suggests a brain hyperarousal state, especially in the emotion-related areas. Thus, patients with insomnia may benefit from modulation of this excessive brain activity. A recent fMRI study indicates that acupuncture can modulate the activity of the cerebro-cerebellar and limbic systems [17].

The aims of this clinical trial are: 1) to determine the effectiveness of acupuncture on sleep quality in patients with insomnia disorder using neuropsychological and rs-fMRI methods; and 2) to elucidate the neurological mechanism by which acupuncture improves sleep quality. In addition to rs-fMRI, actigraphy will also be used to monitor sleep quality by assaying time in bed, sleep latency, waking after sleep onset, sleep time, and sleep efficiency. Patients will be asked to complete sleep diaries and self-report questionnaires, such as the Pittsburgh Sleep Quality Index (PSQI), Hyperarousal scale (HAS), Hamilton Depression Scale **(**HAMD), Hamilton anxiety scale (HAMA), and Fatigue scale-14 (FS-14).

## Methods and design

### Objectives

The study objectives are: 1) to determine the efficacy of acupuncture for the treatment of insomnia disorder; and 2) to elucidate the neural mechanisms for the effects of acupuncture on insomnia disorder.

### Hypotheses

We hypothesize that sleep quality will be significantly improved in the group receiving acupuncture treatment compared with the sham group, as assessed by both subjective (PSQI) and objective (actigraphy) measurements.The hyperarousal state, measured by HAS, will be decreased more in the group receiving acupuncture than the sham group.Based on fMRI examination, functional connectivity and ReHo in the emotion-related areas will be altered in the group receiving acupuncture compared with the sham group.

### Setting

The trial site will be the Acupuncture and Moxibustion Department of the Beijing Hospital of Traditional Chinese Medicine, Capital Medical University, Beijing, China. Sixty patients with insomnia disorder will be assigned to either a real acupuncture group or a sham group, using a digital randomization table in a 1:1 ratio.

### Trial design

This study will be conducted as a single-center, prospective parallel group, patient- and assessor-blinded, randomized controlled trial. The trial will be conducted in accordance with the Consolidated Standards of Reporting Trials [18] and Standards for Reporting Interventions in Clinical Trials of Acupuncture principles [19] to fulfill adequate reporting standards for randomized controlled trials. Sixty patients with insomnia disorder will be assigned to either a real acupuncture group or a sham acupuncture group, using a digital randomization table in a 1:1 ratio. Participants will keep a sleep diary at baseline, during week 4 of treatment, and during week 8 of the follow-up period. Both the neuropsychological measurements and fMRI scans will be performed at baseline, after completion of the acupuncture treatments, and at the conclusion of the follow-up period. Thirty age- and sex-matched healthy individuals who sleep well will be recruited as controls for the fMRI data analysis. All outcome measures will be performed once for the healthy control patients (Fig. 1).

**Fig. 1 Fig1:**
[figure not shown]
Flow chart of study. ALFF amplitude of low-frequency fluctuation, FC functional connectivity, FS-14 Fatigue scale-14, HAMA Hamilton Anxiety scale, HAMD Hamilton Depression scale, HAS Hyperarousal scale, PSQI Pittsburgh Sleep Quality Index, ReHo regional homogeneity, rs-fMRI resting-state functional magnetic resonance imaging

### Participants and recruitment

Posted notices in the hospital and recruitment information on the website of the Beijing Hospital of Traditional Chinese Medicine will be used to recruit study participants.

Participants will be informed about the benefits, as well as possible risks, of participation in the study, including poor clinical outcome and adverse events associated with acupuncture therapy. Completion of consent forms will be compulsory before trial participation and randomization. On the consent form, participants will be asked if they agree to the use of their data should they choose to withdraw from the trial. Participants will also be asked for permission for the research team to share relevant data with people from the hospital taking part in the research or from regulatory authorities. This trial does not involve collecting biological specimens for storage. The model consent form and other related documentation given to participants are available from the corresponding author on request.

A neurologist will determine the PSQI, HAS, HAMD and HAMA scores to decide whether the participants meet the inclusion criteria. Patients who satisfy the inclusion criteria will be randomized (1:1) into either a real acupuncture group or a sham acupuncture group. All participants will complete a baseline rs-fMRI, a 3-day actigraphy test, and a 1-week sleep diary. Participants will receive acupuncture treatment for 4 weeks. In addition, 30 age- and sex-matched healthy individuals who sleep well will be recruited as healthy controls for the fMRI data analysis. All personal information about the participants will be kept confidential by the research investigators and used for research purposes only.

### Inclusion criteria for patients with insomnia disorder

Compliance with the following criteria will be required for participation in the study:
Aged between 20 and 60 yearsMeeting the diagnostic criteria for insomnia disorder according to the Diagnostic and Statistical Manual of Mental Disorders, Fifth EditionA PSQI score >8 points; HAMD score <7; HAMA score <14; and HAS score >32A signed informed consent form specific for this trialHave not received medications for anxiety, depression, or insomnia within 1 month prior to enrollment in the study

### Exclusion criteria for patients with insomnia disorder

Patients will be excluded from enrollment in the trial if they meet one or more of the following:
Diagnosis of anxiety, depression, or schizophreniaDiagnosis of severe medical disorders, including cardiac, cerebral, renal, hepatic, or metabolic diseases, or benign prostatic hyperplasiaDiagnosis of other sleep disorders, such as sleep apnea and restless leg syndromeWomen who are pregnant or breastfeedingDifficulty completing the inspection and treatmentContraindication for MRI including claustrophobia; abnormal signal or obvious asymmetrical head structure by MRIAcupuncture therapy for insomnia treatment in the past monthAddiction to drugs or alcohol

### Inclusion criteria for healthy controls

No complaints about sleep quality and quantityAged between 20 and 60 years of ageA signed informed consent form specific for this trialHave not received medications for anxiety, depression, or insomnia within 1 month prior to enrollment in the study

### Exclusion criteria for healthy controls

Diagnosis of anxiety, depression, or schizophreniaDiagnosis of severe medical disorders, including cardiac, cerebral, renal, hepatic, or metabolic diseases, or benign prostatic hyperplasiaDiagnosis of other sleep disorders, such as sleep apnea and restless leg syndromeWomen who are pregnant or breastfeedingDifficulty completing the inspectionContraindications for MRI including claustrophobia; abnormal signal or obvious asymmetrical head structure by MRIAcupuncture therapy in the past monthAddiction to drugs or alcohol

### Sample size

This study aims to determine the efficacy and central mechanism by which acupuncture affects insomnia disorder. Based on our previous pilot study [20], the PSQI score significantly decreased by 4.43 ± 3.60 in the group treated with acupuncture compared to 1.30 ± 2.58 in the control group. Based on a power analysis, 26 patients per group were required to detect a significant difference (power = 0.9, α = 0.05, two-sided). Thus, we plan on recruiting 30 patients per group to compensate for a 15% drop out rate. There is no known sample size calculation for fMRI research. However, for the exploratory study, 15 to 30 patients are adequate to test the null hypothesis [21, 22].

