### Randomization, allocation concealment, and blinding

After meeting the eligibility requirements, participants will be randomly assigned (in a 1:1 ratio) to the real or the sham acupuncture group. The random allocation sequence will be generated by an independent statistician using Statistical Analysis Software (version 9.3, SAS Institute Inc., Cary, NC, USA). The randomization list will be closed in computer-generated opaque envelopes with sequence numbers printed on the outside of the envelopes. After the patient has been screened, is determined to be eligible, and has given informed consent, the envelopes will be opened by the researchers.

The acupuncturists cannot be blinded and therefore will be excluded from assessments and data processing. In the trial, the participants, data analysts, and outcome assessors will be blinded. Assessors will not perform data analysis. Unblinding should only be performed in case of an emergency, such as any serious adverse events.

In addition, sterile steel needles of the same size and number for each treatment session will be used in both groups. Participants will be required to write down if they have received real acupuncture at the final treatment. The answer ‘Y’ or ‘N’ will be assessed to determine the confidence in the treatment.

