### Primary outcome

Primary outcome is the mean change in PSQI scores from baseline to the end of the treatment period. The PSQI, a self-assessment questionnaire to evaluate sleep quality, will be the primary outcome measurement [25]. The PSQI contains 19 items consisting of seven component scores, including sleep quality, sleep latency, sleep duration, daytime dysfunction, sleep efficiency, sleep disturbances, and sleeping medication. Higher global scores reflect worse sleep quality [26].

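### The stated 26 patients per group at 90% power cannot be reproduced from the printed pilot figures, which need 23; the discrepancy is conservative

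*Protocol article*

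**What the plan says.** The Sample size section of the protocol article bases the calculation on a pilot study in which PSQI scores "decreased by 4.43 ± 3.60 in the group treated with acupuncture compared to 1.30 ± 2.58 in the control group". It gives the design parameters as "power = 0.9, α = 0.05, two-sided" and concludes that "26 patients per group were required to detect a significant difference". It then says "we plan on recruiting 30 patients per group to compensate for a 15% drop out rate". No test, formula or software is named for the power analysis.

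Two other sections fix the remaining inputs. Under Randomization, allocation concealment, and blinding, "participants will be randomly assigned (in a 1:1 ratio) to the real or the sham acupuncture group". Under Primary outcome, "Primary outcome is the mean change in PSQI scores from baseline to the end of the treatment period". The Clinical data analysis section plans to compare group means by repeated-measures analysis of variance, under intention to treat.

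**The concern.** The section prints everything that a comparison of two mean changes needs: both means, both SDs, power, alpha and sidedness. The required number should therefore follow from the text, and it does not. The dropout sentence then builds on that number, and 30 per group does not quite deliver the 26 it is meant to protect.

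This paragraph is the article's only quantitative justification for the size of the randomised comparison. A reader who cannot rebuild 26 cannot tell what margin the trial has, or whether some unstated assumption (a different test, a larger SD, an adjusted alpha) lies behind it.

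**Working it through.** **Inputs.** Mean PSQI decreases are 4.43 (SD 3.60) and 1.30 (SD 2.58); power is 0.90; alpha is 0.05 two-sided; the stated n is 26 per group; dropout is 15%; planned enrolment is 30 per group (all from Sample size). Allocation is 1:1 (Randomization section). The two SDs are weighted equally, as suits 1:1 allocation.

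**Effect size.**
- Difference: 4.43 − 1.30 = 3.13
- Pooled SD: √[(3.60² + 2.58²)/2] = √[(12.96 + 6.66)/2] = 3.132
- d = 3.13/3.132 = 0.999

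**Attempt to reproduce 26.**
- Normal approximation: n = 2(1.960 + 1.282)²/d² = 21.04, so 22 per group.
- Two-sample t test (noncentral t), with Welch's version as a check:

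| n per group | Power, t test | Power, Welch |
|---|---|---|
| 22 | 0.899 | 0.898 |
| 23 | 0.912 | 0.911 |
| 25 | 0.933 | 0.932 |
| 26 | 0.942 | 0.941 |

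The t test needs 23 per group. The stated 26 is 3 more than that, and its power is about 94%, not 90%.

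**Other routes tried, at 90% power.**
- One-sided test: 18 per group.
- Plain average of the two SDs (3.09): 21 (normal) or 22 (t).
- Larger SD, 3.60, in both arms: 28 (normal) or 29 (t); power at 26 would be 0.867.
- Rank test with relative efficiency 0.955: 24.
- Rank test with the minimum efficiency, 0.864: 26 (power 0.906). This does reach the stated figure, but no rank test is mentioned and it does not match the planned analysis of variance.
- 22/0.85 = 25.9, which rounds to 26. This would mean that dropout had already been allowed for once before 30 was derived.

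**Dropout step.**
- From the stated 26: 26/(1 − 0.15) = 30.6, so 31 per group. With 30, 30 × 0.85 = 25.5 remain. Thirty per group keeps 26 only up to a dropout of 4/30 = 13.3%.
- From 23: 23/(1 − 0.15) = 27.1, so 28 per group. Thirty keeps 23 up to a dropout of 7/30 = 23.3%.
- Adding 15% to 26 gives 26 × 1.15 = 29.9, which rounds to the stated 30.

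**The case against.** The strongest reply is that nothing about the trial's adequacy changes. On the pilot figures, 26 per group gives more than 90% power, and so do the roughly 25 per group left after 15% dropout (0.933). Only the word 'required' is inexact. This stands, and it sets the weight of the point.

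It can also be said that the article condenses a fuller protocol in which the derivation of 26 may be found. That is possible, and it is why the conclusion is 'not reproducible as stated' and not a diagnosis of the cause. It does not make the printed inputs and the printed result agree.

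On dropout, the shortfall is one patient per group and exists only relative to 26. Once the requirement is 23, it disappears. The analysis is also by intention to treat with multiple imputation if necessary, so dropouts are not simply discarded. The dropout sentence is therefore a side note.

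Three stronger readings are tempting, and the document does not support them:
- **That 26 came from a 95% power calculation.** The normal approximation at 95% gives 26.02, which rounds up to 27; the t test needs 28; and t-test power at 26 is 0.942. So 26 does not reach 95%, and the text says 0.9.
- **That the allowance was made by multiplying by 1.15.** The arithmetic fits, but no formula is shown, so this is inference.
- **That the trial is underpowered, or that its stated figures cannot coexist.** The discrepancy runs in the conservative direction, and 26 does provide at least the stated power.

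**Conclusion.** The point holds in a limited form. With a difference of 3.13, a pooled SD of 3.13 and a two-sided 5% level, 90% power needs 23 per group by t test (22 by normal approximation). The stated 26 is too high by 3 to 4 per group, and its actual power is about 94%. As a minor addition, 30 per group falls one short of covering 15% dropout from the stated 26, but more than covers it from 23.

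This rests on reading the calculation as a two-sample comparison of mean changes with the printed SDs, which is what the stated inputs and the primary outcome imply. On those assumptions planned enrolment is sufficient. What needs correcting is the stated justification, not the size of the trial.

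**What to change.** Keep 30 per group and restate the calculation in one of two ways.

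1. If the printed inputs are the intended ones, write for example: *With a difference of 3.13 and a pooled SD of 3.13, a two-sided 5% t test needs 23 per group for 90% power; 30 per group with 15% dropout leave about 25, giving power of about 93%.*
2. If 26 came from another test, SD, alpha or power, state those inputs and compute the dropout allowance as n/(1 − 0.15). With 26 retained, that gives 31 per group, so the text should either say so or state that 30 covers a dropout of up to 13.3%.

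The first option costs two sentences and no change in enrolment. The second also leaves enrolment unchanged if the dropout statement is adjusted instead of the number recruited.

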### Ethics

Protocol approval was obtained by the Medical Ethical Committee of Beijing Hospital of Traditional Chinese Medicine on 12 March 2018 (2018BL-002-02). Written informed consent will be attained from each participant. This trial is funded by the National Natural Science Foundation of China (81,774,391, 81,871,507).

### Randomization, allocation concealment, and blinding

After meeting the eligibility requirements, participants will be randomly assigned (in a 1:1 ratio) to the real or the sham acupuncture group. The random allocation sequence will be generated by an independent statistician using Statistical Analysis Software (version 9.3, SAS Institute Inc., Cary, NC, USA). The randomization list will be closed in computer-generated opaque envelopes with sequence numbers printed on the outside of the envelopes. After the patient has been screened, is determined to be eligible, and has given informed consent, the envelopes will be opened by the researchers.

The acupuncturists cannot be blinded and therefore will be excluded from assessments and data processing. In the trial, the participants, data analysts, and outcome assessors will be blinded. Assessors will not perform data analysis. Unblinding should only be performed in case of an emergency, such as any serious adverse events.

In addition, sterile steel needles of the same size and number for each treatment session will be used in both groups. Participants will be required to write down if they have received real acupuncture at the final treatment. The answer ‘Y’ or ‘N’ will be assessed to determine the confidence in the treatment.

**Fig. 2 Fig2:**
[figure not shown]
Enrollment schedule, treatment, and outcome measures. FS-14 Fatigue scale-14, HAMA Hamilton Anxiety scale, HAMD Hamilton Depression scale, HAS Hyperarousal scale, PSQI Pittsburgh Sleep Quality Index, rs-fMRI resting state functional magnetic resonance imaging

**Table 1 Tab1:** Locations and manipulations of real and sham acupuncture

Group	Acupoints	Locations	Needle insertion	Needle manipulation
Real acupuncture group	Baihui (GV-20)	On the head, 5B-cun superior to the anterior hairline, on the anterior median line	Oblique needle insertion at depth of 10 mm	Manipulation and De-qi sensation felt by practitioner and patient
	Shenting (GV-24)	On the head, 0.5B-cun superior to the anterior hairline, on the anterior median line		
	Benshen (GB-13)	On the head, 0.5B-cun superior to the anterior hairline, 3B-cun lateral to the anterior median line		
	Sishencong (EX-HN-1)	Four points at the vertex of the scalp, grouped around Baihui GV-20 and located 1 cun anterior, posterior and lateral to it		
	Neiguan (PC-6)	On the anterior aspect of the forearm, between the tendons of the palmaris longus and the flexor carpi radialis, 2B-cun proximal to the palmar wrist crease	Perpendicular needle insertion at depth of 5 mm	
	Shenmen (HT-7)	On the anteromedial aspect of the wrist, radial to the flexor carpi ulnaris tendon, on the palmar wrist crease		
	Sanyinjiao (SP-6)	On the tibial aspect of the leg, posterior to the medial border of the tibia, 3B-cun superior to the prominence of the medial malleolus	Straight needle insertion at depth of 10 mm	
Sham acupuncture group	Binao (LI-14),	On the lateral aspect of the arm, just anterior to the border of the deltoid muscle, 7B-cun superior to LI-11	Superficial needle insertion at depth of 1 mm	No manual stimulation and De qi sensation
	Shousanli (LI-10)	On the posterolateral aspect of the forearm, on the line connecting LI-5 with LI-11, 2B-cun inferior to the cubital crease		
	Yangchi (TE-4)	On the posterior aspect of the wrist, in the depression ulnar to the extensor digitorum tendon, on the dorsal wrist crease		
	Waiguan (TE-5)	On the posterior aspect of the forearm, midpoint of the interosseous space between the radius and the ulna, 2B-cun proximal to the dorsal wrist crease		
	Fengshi (GB-31)	On the lateral aspect of the thigh, in the depression posterior to the iliotibial band where the tip of the middle finger rests, when standing up with the arms hanging alongside the thigh		
	Liangqiu (ST-34)	On the anterolateral aspect of the thigh, between the vastus lateralis muscle and the lateral border of the rectus femoris tendon, 2B-cun superior to the base of the patella		
	Futu (ST-32)	On the anterolateral aspect of the thigh, on the line connecting the lateral end of the base of the patella with the anterior superior iliac spine, 6B-cun superior to the base of the patella		

